**Fig. 2 Fig2:**
[figure not shown]
Data collection schedule for the CRBP-TS Study (SV: screening visit; EDTA: Ethylenediaminetetraacetic acid; PYTPAQ: Past Year Total Physical Activity Questionnaire; OHIP: Oral Health Impact Profile questionnaire; QLQ-C30: Quality of Life; FSS: Fatigue Severity Scale; PHY2 & 9: Patient Health Questionnaire; WHO-5: well-being index; ESP: electronical cross-sectoral patient file)

The recorded parameters will be stored in the ESP by the cCP or entered by the patients themselves via online questionnaires. To enable the measurement of secondary outcomes, patients from the IG and the CG will receive a wearable device, which will quantify the activity behavior during the entire study period.

At the instruction course (appointment 1b), all patients will receive information about the study program and about the handling of the software and hardware components (tablet with CRBP-TS application, wearable device, instructions about the CRBP-TS application) in small groups.

After 3 months, the first follow-up examination (appointment 2) will be conducted, which will include an incremental exertion test, laboratory analysis (clinical chemistry, tumor markers, inflammation panel), and bioimpedance measurement.

In the final examination (end of the study, appointment 3) after 6 months, all examinations performed at baseline will be repeated.

After 12 months, another follow-up examination (appointment 4) will be conducted in which the measurements from appointment 2 will be repeated.

During the intervention period, physical activity in the IG and the CG will be recorded by a fitness tracker. This assessment will include total calories, resting metabolic rate, number of steps, heart rate (during the training intervention), and sleep quality (length and duration of sleep phases).

In addition, patients will record the intake of their medications using binary confirmation (medications taken or not taken) every morning via the CRBP-TS application. All data will be automatically transferred to the ESP.

The baseline examination (appointment 1a) will include the following measurements.
*Incremental exertion test*

Cardiopulmonary exercise testing to assess oxygen uptake (VO_2_) and maximal power output will perform on an electronically braked semi-recumbent ergometer. The initial load will be 30 W with 10 W/min increments until subjective or objective exhaustion or the occurrence of the termination criteria [30]. After the exercise period follows a 5-min recovery period. Measurement parameters will include ventilation, oxygen uptake (breath by breathy analysis, Dynostics, Sicada GmbH, Germany), oxygen saturation, heart rate (electrocardiogram), blood pressure, cardiac output (measured by impedance cardiography, PhysioFlow Q-Link, Manatec Biomedical, France), blood lactate concentration and rating of perceived exertion. Measurement of cardiac output will not be performed in patients with contraindication to impedance measurement (pacemakers).
2.*Endothelial function*

Flow mediated dilation will be measured by the determination of diameter and flow velocity in the brachial artery before and after forearm compression above systolic pressure for 5 min [31].
3.*Anthropometry*

Height and body mass will be used to calculate body mass index and body surface area. Waist circumference will be assessed at the mid-point between the iliac crest and lowest rib according to standard techniques. Segmental bioimpedance measurement will be measured to calculate lean body mass and fat mass.
4.*Clinical chemistry and inflammation marker panel*

Blood sampling will be performed from baseline (V1) to 6 months (V3) to enable translational research and to assess potential predictive factors of outcomes. Ethylenediaminetetraacetic acid plasma, serum and cell-free DNA BCT® will be collected, centrifuged, and stored at − 80 °C until analysis. Inflammatory cytokine levels, immune cell assessment, high-sensitive C-reactive protein, and tumor necrosis factor alpha will be quantified. Adipose and metabolic markers will include hemoglobin A1c, leptin, adiponectin, insulin, and c-peptide.
5.*Tumor markers and liquid biopsies*

Tumor entity-specific microRNA, circulating free DNA, and circulating tumor DNA; prostate-specific antigen; carcinoembryonic antigen; carbohydrate antigen 15–3; and carbohydrate antigen 19–9 will be determined.
6.*Questionnaires*

The questionnaires will include entity-specific quality of life (EORTC QoLQ-C30), depression (yes/no type Patient Health Questionnaire-2 and Depression Anxiety Stress Scale), and fatigue (Fatigue Severity Scale) risk screening for colorectal, breast, and prostate cancer. Preoperative leisure activity (Past Year Total Physical Activity Questionnaire), WHO-5 (well-being index) and dental care/periodontal status (Oral Health Impact Profile questionnaire) will also be recorded.

### Intervention

#### Intervention group

Using the CRBP-TS application, patients from the IG will receive a complex training and lifestyle improvement program. The exercise training will consist of indication-specific, individualized, heart rate-limited, and online-supported strength-endurance home training with primary focus on improving oxygen capacity using video presentations calibrated according to oxygen consumption. Individual entry and follow-up levels will be used. The follow-up levels will be based on patients’ individual performance development measured by their wearable devices. All exercise adaptions will be supervised by the cCP team.

Details of the training intervention (2–3 times per week for 30 min) are as follows.
Individualized video-home training with feedback information to patients and the cCP: The strength-endurance training based on the initial examination using an online video presentation with indication-specific focuses. Four rounds with five different body-weight exercises (upper and lower body) with 40 s loading and 20 s of recovery phase will be performed. Between rounds there will be a 60 s break. The intensity of the exercise is individually adjustable. Training videos will be changed and modified weekly to provide training variety, and progression.Individualized outdoor endurance training: Depending on patients’ interests supervised endurance training (such as jogging, walking, cycling, fitness facilities, rehabilitation sports) with activity recording and heart rate monitoring should be implemented.

Details of the lifestyle intervention and patient empowerment are as follows.
Structured information on general health improvement, disease prevention, and lifestyle changes (diet, exercise, anti-inflammatory prophylaxis, new therapy options, fatigue, depression, and self-perception) provided by the cCP team via the CRBP-TS application.Advice and appointment reminders (such as reminders about taking medication or failed training) via short message service or e-mailOnline feedback of key parameters (training success in strength and endurance training, performance, heart rate)

During the 6-month intervention, patients will have regular appointments with their outpatient physicians. All physicians will be able to access the ESP and the data summaries including the online monitoring and training data. The outcomes will be discussed with the patients if needed. An interdisciplinary online conference will be conducted every 4 months, which will include family doctors, medical specialists, and the cCP team.

#### Control group

Patients in the CG will receive standard care over a period of 6 months. After inclusion, they will receive general information about necessary lifestyle changes according to the current guidelines. Further course of the study will be analogous to the course followed by the IG.

### Safety analyses

The safety assessment includes observation and recording of any grade of adverse events (AE) and serious adverse events (SAE) during the study, as well as the results of laboratory analyses and clinical examination. Participants in the exercise training group will also be asked about the occurrence of an AE at each training session. The researchers are responsible to take appropriate measures for the AE and determine the causal relationships between the adverse events and the exercise intervention.

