### Individual study plan, measurements, and data collection

A period of 6 months is planned for the recruitment of participants. The intervention period will be of 6 months. Data collection will be performed at baseline (appointment 1a will include examinations and appointment 1b will include instruction course), at 3 months (appointment 2), and at 6 months (appointment 3, end of the study). After 12 months, a follow-up investigation (appointment 4) will be conducted. The IG will undergo individual training intervention and counseling, while patients from the CG will be provided with standard care as well as comprehensive information regarding health-promoting measures. The daily activity of patients in the IG and the CG will be measured and evaluated by the CRBP-TS application. An overview of the examinations during the study visits is shown in Fig. 2.

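### Adverse events are asked about at every training session in the intervention group only, so by-arm counts of reported (chiefly minor) events are open to unequal ascertainment

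*Protocol article*

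**What the plan says.** The Safety analyses section opens with a rule that covers the whole study: "The safety assessment includes observation and recording of any grade of adverse events (AE) and serious adverse events (SAE) during the study". It counts laboratory and examination findings as safety data too. It then adds a second route of collection for one arm: "Participants in the exercise training group will also be asked about the occurrence of an AE at each training session". The word for an addition (also) places the session enquiry on top of the common rule.

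The frequency of that second route follows from the Intervention group section ("Details of the training intervention (2–3 times per week for 30 min) are as follows") and from the individual study plan ("The intervention period will be of 6 months"). The scheduled post-baseline appointments in the same period are "at 3 months (appointment 2), and at 6 months (appointment 3, end of the study"), with one further follow-up at 12 months.

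For the other arm, the Control group section says "Patients in the CG will receive standard care over a period of 6 months". It describes no study training sessions. It says that the rest of the control patients' course parallels that of the intervention group, but it does not mention AE questioning.

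**The concern.** How often patients are asked affects how many mild events are reported. Because events of any grade count, the rule collects the kind of event that depends most on being asked: soreness, a minor strain, a passing symptom. If one arm is asked several times a week and the other has no described enquiry beyond the general rule, the two counts come from different measurement processes.

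An excess of minor AEs under training could then reflect a real effect, the extra questioning, or both, and the data would not separate them. The expected direction is against the intervention. Analysis cannot repair this afterwards, because it cannot recover control-group events that nobody asked about.

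**Working it through.** The plan states no AE rate and no AE comparison figure, so there is nothing to reproduce. The check has two parts.

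**1. Occasions on which AEs are asked about, per patient, during the intervention period**

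Inputs: 2–3 sessions per week (Intervention group section); 6 months (individual study plan), taken as 26 weeks; common appointments at months 3 and 6.

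- Intervention group, session enquiries: 2 × 26 = 52 to 3 × 26 = 78, assuming full adherence. At half adherence: 26 to 39.
- Control group, session enquiries: none, since no sessions are described.
- Scheduled visits common to both arms: 2.

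**2. What unequal capture would do if the true risk were equal (illustration only)**

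Formula: reported risk = true risk × probability that an event is captured. With equal true risk, the reported ratio is the ratio of the two capture probabilities, whatever the true risk. The capture probabilities below are assumptions; the document gives none.

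| Assumed capture, intervention vs control | Reported risk at an assumed true risk of 30% | Reported ratio |
|---|---|---|
| 90% vs 90% | 27% vs 27% | 1.00 |
| 90% vs 70% | 27% vs 21% | 0.9/0.7 = 1.29 |
| 90% vs 50% | 27% vs 15% | 0.9/0.5 = 1.80 |

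To see whether such differences would stand out in a trial of this size, take 150 patients per arm (300 randomised 1:1) and a two-sided 5% comparison of proportions. The chance of a significant difference is approximately Φ[(d − 1.96·s₀)/s₁], where d is the difference in reported risk, s₀ = √(2·p̄(1−p̄)/150) and s₁ = √((p₁(1−p₁)+p₂(1−p₂))/150).

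- 27% vs 21%: d = 0.06, s₀ = 0.0493, s₁ = 0.0492, giving about 23%.
- 27% vs 15%: d = 0.12, s₀ = 0.0470, s₁ = 0.0465, giving about 73%.
- Over assumed true risks of 20% to 50%: about 16–42% for 90% vs 70%, and about 52–96% for 90% vs 50%.
- With equal capture it is the nominal 5%.

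The document plans no such test. The figures only show that moderate differences in capture could produce a visible contrast between the arms with no true difference.

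**The case against.** **No between-arm AE comparison is planned.** AE rates are not among the listed endpoints. The statistical section does not mention AEs, and the safety section ties AE collection to taking action and judging whether events are related to the exercise. On that reading, session enquiries are exercise surveillance and belong only where there is exercise. This stands in part: the enquiries are legitimate and should stay. But a randomised trial ordinarily reports AEs by arm, and a purely descriptive table would carry the same imbalance.

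**Tabulation by source is usual detail for an analysis plan that is not shown.** This also stands in part. Nothing says that session reports will be pooled with the rest, and listing them separately could be specified there. Whether control patients are asked at all is a matter of collection, though, and an analysis plan cannot supply it later.

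**Control-group capture may be better than it looks.** The article does not say how AEs are elicited under the general rule, and both arms are followed by the same care-point teams with the same app. This stands as a limit on certainty. The statement that the control course is parallel does not close the gap, because an enquiry tied to training sessions cannot apply where there are none.

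**Stronger readings.** A reader might infer that every safety comparison is biased, that the intervention-group rate is bound to be inflated, or that no real harm could be recognised. The document does not support these. Laboratory and examination findings at common visits do not depend on session questions, and SAEs and re-hospitalisation depend on them much less. Nor does the safety section say whether those who judge causality know the allocation, so the point does not rest on unblinded assessment.

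**Conclusion.** The point holds in a limited form. The article fixes an AE enquiry at each session for the intervention group and describes nothing equivalent for controls: about 52–78 extra enquiries per fully adherent patient over 26 weeks. Any by-arm comparison of reported AEs, chiefly minor and self-reported ones, is open to differential ascertainment, with the intervention-group count expected to be raised relative to control.

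The direction rests on two assumptions: that being asked more often raises reporting of minor events, and that no control-group enquiry of similar intensity exists outside the article. The size cannot be computed from the document, and the ratios of 1.29 and 1.80 are illustrations under assumed capture rates. The primary endpoint is untouched. This is a cheap improvement that should be made, not a fault that undermines the trial.

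**What to change.** - Put one identically worded AE question to both arms through the CRBP-TS application at the same fixed interval (for example weekly) for the whole intervention period.
- Base any by-arm comparison of reported AEs on that prompt plus the common appointments.
- Keep the session enquiries, and report their yield as a separate intervention-group listing of exercise-related events, outside the comparison. An event raised at a session enters the comparison only if it is also captured by the common prompt or at a common visit.
- State these rules in the protocol and in the analysis plan.

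The cost is one app prompt, a formal amendment (which the Study design section requires for any modification) and a small extra patient burden. All patients already receive the tablet with the app, and the study plan already uses it for a daily entry: "patients will record the intake of their medications using binary confirmation (medications taken or not taken) every morning via the CRBP-TS application". The Trial status section says that recruitment began in August 2020, so if the prompt starts mid-trial, the comparison should cover only the time after its introduction. The change removes the main asymmetry, not all of it: patients questioned at each session may still be readier to answer yes to the common prompt.

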## Discussion

The main objective of this prospective randomized controlled study is to evaluate the systematic use of a home-based physical training and lifestyle intervention module with a multidirectional online monitoring tool supervised by specific clinic staff. Monitoring will include therapy adherence, physical and mental capacity, and efficiency of lifestyle changes. The exemplary care will be planned and continuously adapted at the cCPs consisting of specialized staff (doctor, cancer nurse, sports scientist) based on the ESP files that include findings, training, and measurement data.

Several studies on colorectal, breast, and prostate cancer patients have shown that physical training results in a 20–40% relative risk reduction for recurrence and tumor-associated mortality [6–12]. Therefore, guidelines consistently include the systematic use of physical training in postoperative therapy, with high relevance for the majority of the tumor entities. A balanced combination of strength and endurance training would be highly effective in reducing short-term and intermediate-term tumor-associated morbidity, recurrence, and metastases [18]. Positive effects have also been demonstrated for general cancer symptoms and comorbidities [13, 15, 17]. The existing literature primarily consists of questionnaire surveys based on instructions for lifestyle changes and qualitative implementation of the training programs. Despite the protective, therapeutic, and regenerative efficiency of physical training, a systematic implementation strategy is still lacking. Although physical training also results in significant improvement in several comorbidities, this effective therapy option is currently not used to its full potential.

Essential factors for motivation and high adherence to a training intervention include constant supervision, individual dosage based on personal requirements (overweight and joint problems), and fewer impediments (distance, shame). The best results can be expected from a permanent connection between instructors and patients, preferably online. A supervised program guidance is beneficial for most patients [32]. Additionally, patients should also be able to follow their performance development and clinical findings to maintain motivation. This requires bidirectional online communication, a comprehensible presentation of all findings, and telephone communication with patients if necessary. Objective activity monitoring must be integrated into the process.

CRBP-TS address these issues and offer a cross-sectoral implementation of monitoring, training, and lifestyle (patient empowerment) based on a comprehensive online application (CRBP-TS application). This care structure is independent of patients’ individual living conditions and offers safety and efficiency even in rural areas. In addition to the home-based online intervention, the CRBP-TS study includes comprehensive general and tumor-specific diagnostics (cardiopulmonary performance, liquid biopsy, metabolism, tumor marker panel, circulating tumor DNA, circulating microRNA, and cytokines).

Current studies have shown a correlation of periodontitis with an increased general [33–35] and entity-specific mortality risk for breast, colon, rectum, and prostate carcinomas [34, 36–42]. Therefore, dental screening is also a part of the present study.

To the best of our knowledge, this is the first randomized and prospective study focusing on cardiovascular and metabolic outcomes as well as molecular genetic effects based on the quantified dosage of therapeutic training for CRBP tumor entities. Due to increasing incidence of malignant diseases, poor prognosis, and considerable impairment in the quality of life, there is a need for improvement in cancer care. CRBP-TS project is of economic as well as of social and ethical importance. Due to the short observation period of 6 months and the correlation between mortality and exercise capacity, VO_2_ max will be used as the primary endpoint. Mortality and recurrence rate will be observed as secondary endpoints, requiring longer follow-up.

### Trial status

Protocol version - Date and version identifier: Issue Date 30 March 2020.

The recruitment started in August 2020 and will be approximately completed in June 2021.

## Data Availability

The datasets generated during the present study can be obtained from the corresponding author on reasonable request. The trail results will be communicated via publications.

## Abbreviations

AE: Adverse event
cCP: Cross-linked care points
CG: Control group
CRBP-TS: Colorectal, Breast, and Prostate Cancer - Telemonitoring and Self-management
CRF: Case report form
DNA: Deoxyribonucleic acid
EDTA: Ethylenediaminetetraacetic acid
EORTC: European Organization for Research and Treatment of Cancer
ESP: Electronic cross-sectoral patient-file
FSS: Fatigue Severity Scale
IG: Intervention group
kcal: Kilocalorie
LTE: Long Term Evolution
min: Minute
OHIP: Oral Health Impact Profile
PHY2 & 9: Patient Health Questionnaires
PYTPAQ: Past Year Total Physical Activity Questionnaire
QoLQ-C30: Quality of life questionnaire
RNA: Ribonucleic acid
SAE: Serious adverse event
VO_2_max: Maximal oxygen uptake
WHO-5: World Health Organization well-being index
